#### H1d

Relatively more severe EF deficits and biases at baseline will predict slower improvements in functional outcomes over and above substance use, treatment engagement, and healthcare utilization.

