### Methods and planned analyses

#### Design and participants

The CDiA Program aims to recruit a total sample of 400 adults seeking treatment for AUD and/or SUD to participate in this observational, longitudinal study involving clinical and cognitive assessments at baseline and at a one-year follow-up period (see **Table 1** for a comprehensive list of clinical and cognitive assessments and the time points of each assessment). Inclusion criteria are: (1) 18 - 60 years of age; (2) meeting diagnostic criteria for a current (past year) AUD and/or SUD (not counting nicotine- or caffeine-related disorders); and (3) seeking support for substance use concerns. Exclusion criteria include: (1) acute intoxication or withdrawal; (2) active psychosis; (3) acute suicidality; and (4) history of severe head injury, dementia, severe neurodevelopmental disorders, and other medical conditions or medications that could severely impair cognition.

**Table 1 T1:** Schedule of clinical & cognitive assessments.

Procedure	Construct Measured	Baseline ^a^	Follow up ^b^	Year End ^c^
Informed Consent	N/A	✓		
Verbal confirmation of 12-hour abstinence and time of last substance use	Substance Use	✓		✓
Urinalysis and Breathalyzer	Substance Use	✓		✓
Performance-Based Measures				
CNS-Vitals ^¢ θ^	Cognitive Functioning: General	✓		✓
Iowa Gambling Task ^¢ θ^	Cognitive Functioning: Decision Making	✓		✓
Delay Discounting Task ^¢^	Cognitive Functioning: Decision Making	✓		✓
Probability Discounting Task ^¢^	Cognitive Functioning: Decision Making	✓		✓
Flanker Task ^¢ θ^	Executive Functioning: Inhibitory Control	✓		✓
N-back Task ^¢ θ^	Executive Functioning: Updating	✓		✓
Switch Task ^¢ θ^	Executive Functioning: Set Shifting	✓		✓
Interview-Based Measures				
Diagnostic Assessment Research Tool (55)^d^	AUD, SUD, and other mental health diagnoses	✓		✓
Timeline Follow Back (56)	Substance Use	✓		✓
Psychiatric Treatment History	Treatment History: Medications	✓		✓
Psychological Treatment	Treatment History: Psychological	✓		✓
Self-Report Measures				
Demographics ^$^	Identity	✓		
Bem Sex Role Inventory (Short Form) (68, 69) ^$^	Identity	✓		
Lifetime substance use history (70) ^$^	Substance Use	✓		
Alcohol Use Disorders Identification Test (71) ^$^	Substance Use and Harms	✓		✓
Drug Use Disorders Identification Test (72) ^$^	Substance Use and Harms	✓		✓
Fagerström Test for Nicotine Dependence (73) ^$^	Substance Use and Harms	✓		✓

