#### Measures

Interview measures will include the Diagnostic Assessment Research Tool (DART (57) to assess SUD and comorbid diagnoses, and the Timeline Follow-Back (TFLB (58) to characterize alcohol and substance use over the past 60 days. Self-report items assessing lifetime history of alcohol and substance use will also be administered, along with measures of severity of alcohol- and substance-related harms (see **Table 1**). We will measure both (a) general EF deficits and (b) biases in these functions associated with emotional and motivational states; both neutral and emotional stimuli are used in our EF tasks. The stimuli for the EF tasks are a pool of happy, neutral, and sad faces from the Karolinska Emotional Directed Faces database (KEDF (59). Each task is administered with trial blocks with emotional stimuli (i.e., to measure EF biases) and trial blocks with neutral stimuli (i.e., to measure EF deficits). A flanker task (60–63) will be used to assess inhibition, an n-back task (64, 65) will be used to assess working memory updating, and a switch task (66) will be used to assess set-shifting.

Global cognitive function will be evaluated with the Central Nervous System Vital Signs (CNS-VS (67) computerized assessment, which has been validated for use in addiction. To minimize the impact of acute intoxication on cognition and EF, we will verbally confirm participants have not used alcohol/substances 12 hours prior to their cognitive assessment (Last Drug Use Verification Form) and administer a breathalyzer test to confirm zero blood alcohol concentration at the time of testing. We will also administer a urine drug screen and collect self-report data on time since last use of each drug to account for recency of use in the analyses. Other factors relevant to understanding substance use patterns are also assessed, including demographic factors, readiness to change, substance use motives, SUD insight, SUD treatment history, and concurrent mental health difficulties. The complete battery of measures is compiled to provide a fulsome characterization of the sample, consistent with the unique perspectives of each CDiA project and with the intended generativity of the CDiA Program for future research (see **Table 1** for a full list of measures).

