### Power analysis and data analytic plan

Multiple regression will be used with the clinical, functional, and demographic factors entered as simultaneous predictors of each EF domain to test hypotheses about which factors are most strongly associated with specific EF domains (H1a and H1b).

For H1c, we will conduct latent profile analyses using domains of EF as indicators of discrete latent profiles of relative deficits and biases. We will then examine the prediction of membership in these latent profiles from substance use profiles.

For H1d, latent growth curve modeling will be used to model changes in substance use frequency, SUD severity, and functional outcomes over the follow up time points. Next, rate of change will be examined as a function of baseline EF (H1a) by regressing variability in the slopes for the growth factors on baseline EF deficits and biases. These will be included as simultaneous predictors in the model to examine the specific EF domains and biases that are most predictive of change in the clinical and functional outcomes.

For H1e, we will use a generalized linear mixed effects modelling approach. EF deficits and biases will be modelled as dependent variables and time will be entered as a within-subjects factor to determine if there is significant within-person change from baseline to one year follow up. Changes over time in SUD symptoms and functional outcomes will be modelled using the same approach, with changes in EFs included in the models as a time-varying predictor of changes in these outcomes.

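### Project 1 plans a latent growth curve for substance use frequency, which is measured at only two occasions; secondarily, the H1d slope regression as written does not test the hypothesis's 'over and above' claim

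*Protocol article*

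**What the plan says.** **Hypothesis.** H1d predicts that worse baseline executive function (EF) goes with "slower improvements in functional outcomes over and above substance use, treatment engagement, and healthcare utilization".

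**Model.** Under Project 1, Power analysis and data analytic plan, "latent growth curve modeling will be used to model changes in substance use frequency, SUD severity, and functional outcomes", across the follow-up visits. The next step is "regressing variability in the slopes for the growth factors on baseline EF deficits and biases". The plan then adds: "These will be included as simultaneous predictors in the model to examine the specific EF domains and biases that are most predictive of change". Project 7, in its section on longitudinal stability of subgroups, again describes Project 1 as relating individual substance use trajectories to baseline EF.

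**Schedule.** In Table 1 the row "Timeline Follow Back (56" is ticked under Baseline and Year End, with the Follow up column empty. AUDIT, DUDIT and the urinalysis/breathalyzer row have the same pattern. Footnote b defines the follow-up visits as months 2, 4, 6, 8 and 10. Of the substance use and functional measures, those ticked there are the Severity of Dependence Scale (SDS), WHODAS 2.0 and WHOQOL-BREF. Project 1, Measures says the Timeline Follow-Back is used "to characterize alcohol and substance use over the past 60 days".

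**Covariates.** The only adjustment stated for all analyses is recency of use, under Limitations.

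**The concern.** A latent growth curve estimates how much people truly differ in their rate of change, and it needs enough occasions to separate those differences from measurement error. With a baseline and a year-end value it cannot do so. Two 60-day windows also leave most of the year unobserved, so no trajectory can be rebuilt from them. One of the three listed kinds of outcome therefore has an analysis that its own schedule does not support, and the analysts would have to choose a substitute after the data are in.

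The second matter is a mismatch between hypothesis and model. H1d claims incremental prediction "over and above substance use, treatment engagement, and healthcare utilization", but the regression that is meant to test it names only EF terms as predictors of the slopes. Substance use appears there as a further outcome, not as a covariate. Project 6, Background argues that EF affects treatment retention and engagement and probably health care use. An EF association from the model as written could therefore partly reflect those factors.

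**Working it through.** The article gives no power or sample-size figure for H1d, so there is no planned figure to reproduce.

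**1. Occasions (Table 1 and its footnotes)**
- Timeline Follow-Back, AUDIT, DUDIT: baseline and month 12, so 2 occasions.
- SDS, WHODAS 2.0, WHOQOL-BREF: baseline, months 2, 4, 6, 8 and 10, and month 12, so 7 occasions.

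**2. Identification of a linear growth model**

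Observed moments for T occasions: T means + T(T+1)/2 variances and covariances. Parameters: 2 factor means + 2 factor variances + 1 factor covariance + residual variances (T if free, 1 if held equal, 0 if fixed at zero).

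| Occasions | Residual variances | Moments | Parameters | df | Identified |
|---|---|---|---|---|---|
| 2 | free | 2+3 = 5 | 5+2 = 7 | -2 | no |
| 2 | equal | 5 | 5+1 = 6 | -1 | no |
| 2 | fixed at zero | 5 | 5 | 0 | just identified |
| 7 | free | 7+28 = 35 | 5+7 = 12 | 23 | yes |
| 7 | equal | 35 | 5+1 = 6 | 29 | yes |

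Adding EF predictors does not help. Take six (three deficits and three biases, an assumed count). Each adds 2 moments and 2 parameters at two occasions, giving 5+12 = 17 moments against 7+12 = 19 or 6+12 = 18 parameters. A numerical rank check of the model's Jacobian gave rank 5 without predictors and rank 17 with six, short of the parameter count in both cases.

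**3. What two occasions can still give**

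With predictors x, E[y1 | x] gives the effect on the starting level, and E[y2 | x] - E[y1 | x] gives the effect on change. The unstandardised coefficient of change on EF is therefore estimable; the rank check confirms this. What cannot be estimated are the slope variance net of error, the shape of change and model fit.

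**4. Leaving out an H1d factor**

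The documents give no correlations, so these values are assumed. Let EF correlate rho with the omitted factor, let that factor have standardised effect b on the slope, and let EF have no effect of its own. The expected EF-slope correlation is then r = rho x b. The two-sided 5% test rejects with probability 1 - Phi(1.96 - z) + Phi(-1.96 - z), where z = atanh(r) x sqrt(n - 3). At n = 400, sqrt(397) = 19.92.

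| rho | b | r | Rejection rate |
|---|---|---|---|
| 0.1 | 0.1 | 0.01 | 5.5% |
| 0.2 | 0.2 | 0.04 | 12.5% |
| 0.2 | 0.3 | 0.06 | 22.4% |
| 0.3 | 0.3 | 0.09 | 43.6% |

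This treats the slope as observed and assumes all 400 participants are retained. At an assumed 320 retained, the range is 5.4% to 36.2%.

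**The case against.** **H1d's own outcomes are unaffected.** H1d concerns functional outcomes, and those have seven occasions, as does the SDS for severity. This stands. Substance use frequency is an additional outcome brought in by the analysis section.

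**Two-occasion change can still be regressed on EF.** This also stands. A reader might infer that no analysis of use frequency is possible, or that measurement error will bias the EF effect towards zero. The documents support neither. Fixing the residual variances at zero gives a just-identified change-score model. Random error in change costs precision and shrinks standardised correlations, but it does not bias the unstandardised coefficient. That model is nevertheless not the growth curve the article announces.

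**A condensed article need not list every covariate.** This stands in part. The analysis section does not say that EF terms are the only predictors, and it omits recency of use even though the Limitations section applies that to all analyses, so its list is evidently incomplete. But recency is there to handle residual drug effects on cognition. It is neither frequency of use nor engagement nor health care utilization. Since H1d makes the incremental claim explicitly, the model described for it should carry the terms that test it.

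**Some of these factors may be mediators.** This stands. If EF acts on functioning through engagement or use during the year, the unadjusted association is a genuine total effect. Adjusting for baseline values alone would not remove those pathways.

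**Conclusion.** The growth curve planned for substance use frequency is not identified under the article's own visit schedule: 5 moments against 6 or 7 parameters. This follows by counting and needs no assumption beyond a linear model with residual variance. It affects that one outcome only.

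The covariate point is smaller. The slope regression as described does not by itself test H1d's incremental claim. How much this matters depends on correlations that the documents do not give: the rejection rate runs from about 5.5%, barely above nominal, to about 44% at n=400 over the assumed range. A reader might take the upper figure as the expected false-positive rate, or conclude that H1d cannot be tested at all. Neither follows. The upper figure needs both assumed values at 0.3, and the functional-outcome growth models can be fitted and extended with covariates that the program already plans to hold.

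**What to change.** 1. **Growth models.** Restrict them to the SDS, WHODAS 2.0 and WHOQOL-BREF.
2. **Use frequency.** Analyse year-end days of use from the Timeline Follow-Back (0 to 60) with a count or beta-binomial regression on baseline EF, adjusted for baseline days of use. Align the Project 7 description of substance use trajectories with this.
3. **H1d functional-outcome model.** Add substance use, treatment engagement and healthcare utilization as covariates, state when each is measured, and report the EF coefficients with and without them. State that factors measured during follow-up may be mediators, so the adjusted and unadjusted results answer different questions.

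**Cost.** This is analysis-plan wording. The data are already planned: substance use and treatment interviews in Table 1, and health care records through the Project 6 linkage. The loss is that no trajectory shape will be available for use frequency. Keeping one would require collecting frequency at the bimonthly visits, which adds burden and cannot be done for visits already past. The covariates should be fixed before analysis, so that their inclusion is not a post hoc choice.

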#### H1e

EF domains will show improvements from baseline to the one-year follow-up. Improvements in EF will be positively associated with improvements in SUD symptoms and in functional outcomes.

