##### Cognitive fMRI paradigms

We administer three EF tasks for a total duration of ~30 minutes. The tasks assess the same EF domains as in P1 but were specifically selected to be distinct from the paradigms used in P1 to reduce practice effects, which may alter in-scanner performance and brain activation patterns (121, 122). The EF cognitive paradigms were adapted from Rieck et al. (92) and are presented in a pseudorandom order counterbalanced across participants. To minimize visual distraction and permit joint analysis across all EF dimensions, the tasks were designed to be visually simple and consistent across EF domains, using white or light-colored letter stimuli against a dark grey background (**Figure 2**).

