### Clinical assessments

Participants will be initially screened with the MINI and C-SSRS. Interested and potentially eligible participants will complete a subsequent interview to address all criteria outlined above to confirm eligibility. The 17-item Hamilton Rating Scale for Depression (HRSD-17) (168) will be our tertiary clinical outcome measure. The tertiary clinical outcome criteria will be a decrease in HRSD-17 score at treatment end compared to baseline (150, 162). The HRSD-17 will be performed at baseline, weekly and at the end of the rTMS treatment course. The Columbia-Suicide Severity Rating Scale (C-SSRS) will be used to evaluate suicidality. This reliable and valid scale has been used in randomized clinical trials and is able to predict completed suicide (169). The C-SSRS has been reported as an effective measure for diagnosis and treatment across several diagnoses (170–172) with high internal consistency, and interrater reliability (172–176). The C-SSRS will be performed at baseline, weekly and at the end of the rTMS treatment course. TMS Adult Safety Screen (TASS) (166) will be used at recruitment and baseline to ensure that participants are safe to participate in rTMS treatment trials. To enhance integration with other projects, we will re-administer the EF cognitive assessments within one week prior to the start of rTMS and at the end of the 4-week course of rTMS.

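### H1e's mean EF improvement is tested only by a time effect in one cohort repeating the same tasks, so for EF-deficit scores a significant rise cannot be told apart from a retest gain

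*Protocol article*

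**What the plan says.** H1e in Project 1 makes two statements. The first concerns the mean: "EF domains will show improvements from baseline to the one-year follow-up". The second concerns association: "Improvements in EF will be positively associated with improvements in SUD symptoms and in functional outcomes".

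The section Power analysis and data analytic plan tests the first with a mixed model of EF deficits and biases, in which "time will be entered as a within-subjects factor to determine if there is significant within-person change from baseline to one year follow up". For the second, symptoms and functional outcomes are modelled in the same way, with change in EF as a time-varying predictor.

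Under Design and participants, the program "aims to recruit a total sample of 400 adults seeking treatment for AUD and/or SUD" to an observational study "involving clinical and cognitive assessments at baseline and at a one-year follow-up period". Table 1 ticks the flanker task ("Executive Functioning: Inhibitory Control"), the n-back task and the switch task at both Baseline and Year End. Project 1 describes no comparison group, alternate forms, familiarisation session or term for prior exposure. The Limitations section promises adjustment of all analyses for recency of use.

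Practice is considered elsewhere. The Project 2 scanner tasks were "specifically selected to be distinct from the paradigms used in P1 to reduce practice effects". Project 5 argues that its rat tests are stable under repetition and changes the set-shifting rules between sessions. In Project 4, "we will re-administer the EF cognitive assessments within one week prior to the start of rTMS", and again at the end of the four-week course.

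**The concern.** In a single group tested twice on the same tasks, the mean change is true change plus whatever is gained from having done the tasks before. The stated test asks only whether that sum differs from zero. A positive result would be read as EF improving over a year in people seeking treatment, although familiarity alone could produce it. Recency-of-use adjustment deals with residual drug effects, not familiarity.

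Exposure is also uneven. The 40 Project 4 participants take the EF assessments twice more between baseline and year end, and do a 2-back task in two EEG sessions. About 200 people are expected to do three further EF tasks in the scanner. Part of the mean change may therefore depend on which sub-projects a person joined.

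**Working it through.** **Figure to reproduce.** None. The Project 1 section has power analysis in its title but gives no effect size, power or significance level for H1e.

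**Inputs from the article.** Target N = 400; two EF occasions; one group; 40 participants in Project 4, randomised 1:1, so 20 on active stimulation.

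**Inputs assumed.** Two-sided 5% level (0.05 is given for Projects 3 and 4, not Project 1); retest gain d of 0.1, 0.2 or 0.3 SD of the score; correlation r between occasions of 0.5 to 0.8; 400 or 240 completers (100% or 60%). True EF change is set to zero.

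**Step 1: chance that the time effect is significant.** With two occasions the test is equivalent to a paired t-test. The standardised mean change is dz = d / √(2(1 − r)), and the noncentrality is dz × √n.

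For d = 0.2 and r = 0.5, dz = 0.2 / √1 = 0.20. For r = 0.8, dz = 0.2 / √0.4 = 0.316. From the noncentral t distribution:

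| Assumed gain | n = 400, r = 0.5 to 0.8 | n = 240, r = 0.5 to 0.8 |
|---|---|---|
| 0.1 SD | 51% to 88% | 34% to 68% |
| 0.2 SD | 98% to >99% | 87% to 99.8% |
| 0.3 SD | about 100% | >99% |

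An observed dz of 0.098 at n = 400, or 0.127 at n = 240, is already significant. A small retest gain is enough.

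**Step 2: does the same problem reach H1e's second sentence?** Simulation with 300 people, r = 0.7, a uniform 0.2 SD gain in EF, no true EF change, no true association and 2,000 replicates. The proportion of falsely significant associations was:

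| Mean improvement in the outcome | Time in model | Time omitted |
|---|---|---|
| 0 SD | 4.8% | 4.6% |
| 0.3 SD | 5.7% | 24.7% |
| 0.5 SD | 5.3% | 50.1% |

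A uniform gain shifts everyone equally and is absorbed by the time term, so the association test keeps its nominal error. The article says this model follows the same approach as the first, so the natural reading is that time stays in. The table shows why that should be explicit.

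**Step 3: deficits against biases.** Under Measures, deficits come from neutral blocks and biases from emotional blocks. If a bias is scored as emotional minus neutral, a gain equal in both blocks cancels. A deficit score has no such protection.

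**Step 4: where practice is not uniform.** Project 4 admits only people free of problematic use for more than a month. Its two extra administrations therefore go to 40 / 400 = 10% of the target sample, selected partly on reduced use. In that subgroup extra practice and lower use go together, which the time term does not remove. Any effect of active stimulation on EF in 20 of them adds to this.

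**The case against.** The strongest reply has four parts.

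- **H1e is more than its first sentence.** The association analysis already relates EF change to clinical change and is robust to a uniform gain. This stands. A reader might infer that the whole of H1e could be confirmed without any recovery; the documents do not support that.
- **The article does not concede a gain at the one-year retest.** Project 2 chose its tasks to avoid carry-over into the scanner, and the Project 5 remarks concern rats. This stands. A reader might infer that the program admits a practice gain in its own Project 1 outcome, but neither statement says so. The Project 2 choice also limits carry-over in the other direction: scanner stimuli are letters, whereas Project 1 uses faces. Any gain may be smaller after twelve months, though the article does not argue this.
- **The percentages are not evidence about this study.** This stands. They are the power of a paired test under assumed gains, correlations and retention, and must not be read as the study's false-positive rate.
- **The remedy is analysis-plan detail.** This stands only in part. A plan could add retest norms or an exposure term. But the article itself fixes the claim, the single group, the repeated tasks and the test, and the complaint is that this test cannot carry this claim.

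**Conclusion.** The concern holds for the first sentence of H1e and for EF-deficit scores. A statistically significant rise over the year would be compatible with true improvement, retest gain or both, and the analysis as described cannot tell which. The size of the retest gain is unknown from the documents. If it were 0.1 SD with no true change, the time test would be significant in 34% to 88% of studies over the assumed correlations and the two completer numbers; at 0.2 SD, in 87% or more.

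H1e's second sentence is not affected by a uniform gain provided time is in the model. Bias scores may be less affected if practice is equal across emotional and neutral blocks. What is at stake is the interpretation of one Project 1 hypothesis.

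**What to change.** 1. Report the overall time effect on EF as descriptive change that includes practice, not as evidence of EF recovery.
2. Rest the recovery claim on the association of within-person EF change with continuous change in substance use (60-day Timeline Follow-Back) and dependence severity (Severity of Dependence Scale). Both are collected at baseline and year end. State that time is kept in the model.
3. Repeat the analysis without the 40 Project 4 participants, who have two further EF administrations and of whom half receive active stimulation. Add Project 2 scan participation as a sensitivity covariate.

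Two tempting alternatives are best avoided. Splitting participants into reducers and non-reducers discards information that the continuous analysis keeps. Using the Project 4 retest before stimulation to estimate the practice gain is confounded, because those participants must by then have gone more than a month without problematic use, so their change may already include recovery.

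The cost is analysis and wording only, with no new data. The association is less precise than a one-group time effect. It is also not randomised, so it would not prove recovery caused by reduced use.
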